## Abstract

**Background:**

Non-steroidal anti-inflammatory drugs (NSAIDs) and analgesics are used frequently by athletes either prophylactically for the prevention of pain, or to accelerate recovery following an injury. However, these types of pain management strategies have been shown to inhibit signalling pathways (e.g., cyclooxygenase-2) that may hinder muscular adaptations such as hypertrophy and strength. Nutraceuticals such as palmitoylethanolamide (PEA) have analgesic properties that act via different mechanisms to NSAIDS/analgesics. Furthermore, PEA has been shown to have a positive effect on sleep and may contribute positively to muscle hypertrophy via PKB activation. Although PEA has not been widely studied in the athletic or recreationally active population, it may provide an alternative solution for pain management if it is found not to interfere with, or enhance training adaptations. Therefore, the study aim is to investigate the effects of daily PEA supplementation (Levagen + ®) with resistance training on lean body mass, strength, power and physical performance and outcomes of recovery (e.g., sleep) compared to placebo.

**Methods:**

This double-blind, randomised controlled study will take place over an 11-week period (including 8-weeks of progressive resistance training). Participants for this study will be 18–35 years old, healthy active adults that are not resistance trained. Participants will attend a familiarisation (week 0), pre-testing (week 1) and final-testing (week 11). At the pre-testing and final-testing weeks, total lean body mass (dual-energy X-ray absorptiometry; DXA), total mid-thigh cross sectional area (pQCT), maximal muscular strength (1 repetition maximum bench press, isometric mid-thigh pull) and power (countermovement jump and bench throw) will be assessed. Additionally, circulating inflammatory cytokines and anabolic hormones, sleep quality and quantity (ActiGraph), pain and subjective wellbeing (questionnaires) will also be examined.

**Discussion:**

This study is designed to investigate the effects that PEA may have on pre-to post intervention changes in total body and regional lean muscle mass, strength, power, sleep, subjective wellbeing, and pain associated with resistance training and menstruation compared with the placebo condition. Unlike other NSAIDs and analgesics, which may inhibit muscle protein synthesis and training adaptations, PEA which provides analgesia via alternative mechanisms may provide an alternative pain management solution. It is therefore important to determine if this analgesic compound interferes with or enhances training adaptations so that athletes and active individuals can make an informed decision on their pain management strategies.

**Trial registration:**

Australian New Zealand Clinical Trials Registry (ANZCTR: ACTRN12621001726842p).

**Supplementary Information:**

The online version contains supplementary material available at 10.1186/s13063-023-07199-y.

## Background and rationale

Body composition and power-to-weight ratio are acknowledged as key performance determinants in a variety of different sporting modalities [1]. Both variables rely on athletes possessing sufficient skeletal muscle mass (relative to fat mass) and muscle quality (e.g., strength/power relative to muscle mass), and these outcomes differ between sub-elite and elite athletes in a range of different sports [2–5]. For example, lower body fat and higher power-to-weight ratio are important for sports that rely on power, speed, and agility such as martial arts, boxing, gymnastics, and team sports such as soccer and rugby [6, 7]. Additionally, increasing muscle mass is a common pursuit for many recreationally active individuals who aim to optimise their body composition and strength for aesthetic reasons or long-term health (e.g., healthy ageing and metabolic risk factors) [8, 9]. Acknowledging that skeletal muscle mass, strength, and power are key elements in any athletic development program, understanding methods to optimise these outcomes while minimising increases in body fat is of great value to many athletes as well as the general population.

The management of pain arising either from injury (e.g., acute or overuse) or factors associated with exercise and training [such as delayed onset muscle soreness (DOMS)] is important for athletes as it can influence immediate and future performance. Pain management is often overlooked in athletic preparation and athletes that experience pain may lose training time or withdraw from competition altogether [10]. Furthermore, female athletes who experience pain prior to- or during the menstrual phase of their cycle have reported that it negatively impacts their performance during training or competition [11]. Lastly, pain can also affect sleep quality in a reciprocal relationship [12, 13]. For example, athletes that report inadequate sleep time or quality (e.g., restful sleep vs restless) are at increased risk of injury, illness susceptibility, weight gain and decreased pain tolerance [13]. Consequently, athletes report frequently ingesting non-steroidal anti-inflammatory drugs (NSAIDs) prophylactically for the prevention of pain, or to speed recovery following an injury [14–16]. One study reported that elite Olympic level athletes are 3.6 times more likely to use NSAIDs than age-matched controls [17]. Additionally, reports in elite level football players have reported 10–20% of athletes taking NSAIDs either prior to almost every match [18]. Many common pain management agents, such as NSAIDs, ibuprofen, and analgesic paracetamol, reduce pain by inhibiting cyclooxygenase-2 (COX-2) [19–22]. Inhibition of COX-2 negatively affects the anabolic signalling pathways that induce the muscle protein synthetic response to acute exercise, potentially impairing long-term physiological adaptations [19–22]. Therefore, it may be beneficial to explore alternatives to pain management for athletes that do not have the potential negative side effects associated with COX-2 inhibitors.

Nutraceuticals are dietary supplements derived from food sources that have added benefits beyond those obtained from food sources alone [23]. In preliminary studies, nutraceuticals are showing promising benefits in augmenting adaptations in skeletal muscle mass following resistance training either directly or indirectly but are not widely studied in the literature [23, 24]. Palmitoylethanolamide (PEA) is a nutraceutical compound that has supported analgesic effects for both acute and chronic pain [25, 26]. PEA doses of between 300 -1200 mg have been well-tolerated and shown to be effective at reducing pain associated with osteoarthritis, and it can reduce markers of skeletal muscle damage following damaging exercise [26–28]. PEA has both anti-inflammatory and analgesic effects through a variety of receptor sites both directly [e.g., proliferator-activated receptor alpha (PPARα); G protein-coupled receptor 55 (GPR55)] and indirectly [e.g., Cannabinoid receptor type 1 and 2 (CB_1 and_ CB_2_); transient receptor potential cation channel subfamily V member 1 (TRVP1)] [29]. Unlike NSAIDs, ibuprofen, and analgesic paracetamol, which inhibit muscle protein synthesis [30], orally-dosed PEA increases protein kinase B (PKB) phosphorylation following exercise, which plays an integral role in the anabolic pathways promoting skeletal muscle hypertrophy [31]. Additionally, PEA may improve sleep quality and duration, which could further assist athletes’ recovery and therefore will likely be beneficial for athletes [32]. Unlike the negative side effects found in COX-2 inhibitors, the analgesic and anti-inflammatory properties of PEA could provide an alternative solution to pain management as well as contribute positively to muscle hypertrophy and sleep, all of which are likely to be highly beneficial for athletes and active individuals.

### Objectives

The primary aim of this study is to investigate the effects of daily PEA supplementation (Levagen + ®) during an 8-week period of resistance training on pre- to post-intervention changes in total body and regional lean body mass (e.g., mid-thigh) compared with a placebo condition. Our secondary aims are to explore the effects of PEA supplementation on changes in strength, power, sleep, subjective wellbeing, and pain associated with resistance training and menstruation.

### Trial design

This double-blind, randomised controlled study will take place over an 11-week period (including 8-weeks of progressive resistance training). Participants for this study will be 18–35 years old, healthy active adults that are not resistance trained. It is hypothesised that PEA supplementation together with resistance training will further improve muscle mass, strength and power, enhance wellbeing, reduce post exercise muscle soreness and menstrual pains, and improve sleep quality and this effect will be greater than the placebo group.

## Methods: Participants, interventions and outcomes

### Study setting

This study will take place at Deakin University, Burwood campus. This protocol is reported in accordance with the Standard Protocol Items: Recommendations for Intervention Trials (SPIRIT) [33]. Recruitment commenced in March 2022 and is expected to finish in March 2023. This study design, as well as all consent forms and research tools have been approved by Deakin University Human Research Ethics Committee (DUHREC: 2021–312).

### Eligibility criteria

Participants in this study will be males and females between the ages of 18–35 years old who will be recruited via online advertisements (e.g., Facebook) and study posters advertised around the local area. In response to the advertisement materials, interested individuals can: 1) directly email the study coordinator, or; 2) complete an online form which will provide contact details so that research staff can contact them directly. All interested individuals will be screened via telephone to determine eligibility. Participants will be eligible for inclusion into the study if they meet the following criteria:

### Inclusion criteria

Recreationally active (a minimum of 150 min of self-reported moderate-intensity physical activity per week)Stable body mass for the last 2 monthsBMI between ≥ 18.5 or ≤ 28 kg/m.^2^

### Exclusion criteria

Major musculoskeletal injury in the past 6 monthsParticipation in regular structured resistance training in the past 6 months (e.g., two or more sessions per week)Allergies to any of the contents of the Levagen + ® supplement or placebo formulationCurrently participating in a weight loss program or special diet (e.g., Low carbohydrate, ketogenic, vegan etc.)SmokersCurrent functional impairment that would limit participation in the interventionUse of sports supplements (e.g., creatine or protein powder) or pain medication in the last monthCurrent chronic disease including: cancer, diabetes, cardiovascular disease, chronic liver disease, and gastrointestinal disorders that affect nutrient absorptionCognitive impairment or inability to commit to the study and its requirements

Once participants agree to participate, one of the researchers responsible for the study coordination (ZH) will provide the participant with a written plain language explanatory statement as well as verbally describe the study details. Participants will be provided both verbal and written information regarding the following: the purpose of the study, the study aims, the procedures of the study and what will be required from the participant during the 11-weeks, possible benefits and risks for participating, how their data will remain confidential and contact details for any problems concerning the project. During the familiarisation visit, prior to any testing, written consent will be obtained [appendix 1]. Participants will be informed that they are free to withdraw from the study and withdraw their consent at any time during the study [appendix 2]. To further promote study retention, participants will receive a $200 gift card upon completion of the study. During the study, participants will be asked to resume their usual physical activity and dietary habits and be asked to avoid taking any pain medication during the course of the study.

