### Interventions

#### Supplements

Eligible participants will be asked to maintain their usual dietary intake and current exercise habits, abstain from using any pain medication, and sports supplements that are not provided during the course of the study. The intervention groups will be provided capsules of PEA (350 mg/day as 2 × 175 mg Levagen + ® capsules), or identical matching placebo capsules (in colour and weight) containing maltodextrin (2 × 175 mg capsules), which will be taken orally (swallowed) for 8-weeks. On training days, participants will be instructed to take 1 × capsule 45 - 60 min prior to exercise with their standardised meal (388 kcals, 45 g CHO, 21 g PRO, 13 g FAT) and 1 × capsule in the evening 60 min prior to sleep [32]. The supplement taken prior to exercise is provided based on the time to peak blood concentrations of PEA (~ 45–60 min) [34]. On non-training days, participants will be asked to consume 1 × capsule with their morning meal and 1 × capsule pre-sleep, 60-min prior as per training days. The dosage of the supplement within this study is well below previous studies that have shown dosages of up to 1,200 mg/day have no harmful effects [35]. In the rare case that a participant may experience undesirable side effects, the blind will be broken, and participants will be referred to a local general practitioner and they may withdraw from the study.

The trial products will be supplied by Gencor Pacific (Lantau Island, Hong Kong) and manufactured by Pharmako Biotechnologies (Sydney, Australia). Compliance with dosing at home will be assessed by pill count and a tracker sheet at the end of the study.

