Following each resistance training session, participants will be provided with a flavoured whey protein concentrate beverage (250 Cals; 40 g protein) mixed with 200–300 ml of water to be consumed within 15 min of completing the session to support and maximise muscle protein synthesis and promote muscle hypertrophy adaptations.

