#### Muscle strength and power

Prior to any exercise testing participants will be provided with a standardised breakfast (388 kcals, 45 g CHO, 21 g PRO, 13 g FAT).

A force plate (400 s + Performance Force Plate, Fitness Technology, Adelaide, Australia) will be used to assess lower body strength and power during isometric mid-thigh pull (IMTP) and countermovement jump (CMJ) tests, respectively. The force plate will be interfaced with computer software (Ballistic Measurement System; Fitness Technology, Adelaide, Australia). The CMJ outcomes will be jump height (cm), peak force (N), peak power (W). The outcomes for the IMTP will be peak force (N) and peak power (W). Participants will undergo a standardised warm-up prior to performing 3 maximum-effort attempts of the CMJ and IMTP, respectively. The highest value of the 3-maximium efforts for the exercise will be analysed and reported to compare group differences.

Upper body power will be assessed using a bench throw performed using a Smith machine squat rack (Maxrack, IP-L8505, Star trac, Irvine, California, United States). A linear position transducer (GymAware v2.4.1, GymAware, Kinetic Performance Technology, Canberra, Australia) will be attached to the Smith machine barbell and used to assess barbell velocity (m/s) and power (W). Following a standardised warm-up, participants will perform 3 sets of 4 repetitions with a 2-min rest interval between sets. The highest value for the 3-maximum attempts for peak velocity (m/s) and peak power (W) will be recorded for each participant.

Lastly, upper body strength will be assessed by a 1-repetition maximum (1-RM, kg) bench press using a free weight bench press. Participants will first perform a warm-up involving 8, 5, and 3 repetitions with 50%, 75%, and 95% of predicted 1-RM, respectively. Participants then will perform 1-RM attempts with increasing loads (5–10 kg for males; 2.5–5 kg for females), with a 2.5 kg minimum load, until the 1-RM is reached. Participants will rest for 3 min in-between sets [38].

For all strength and power performance outcomes, the mean group difference at pre-testing vs post-testing will be reported.

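### The allergy exclusion names only the capsules, although the trial also gives every participant whey protein and a standardised meal, so a milk-allergic volunteer could be enrolled

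*Protocol article*

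**What the plan says.** The Exclusion criteria section of the protocol article contains one item on allergy. It begins "Allergies to any of the contents of the Levagen" and ends with the placebo formulation. The Supplements section describes the comparator as "identical matching placebo capsules (in colour and weight) containing maltodextrin".

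Participants in both arms are also given two other products:

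- **Whey beverage.** Under Resistance training, after each session "participants will be provided with a flavoured whey protein concentrate beverage" providing 40 g of protein, "to be consumed within 15 min of completing the session".
- **Standardised meal.** Under Supplements, one capsule on training days is taken "prior to exercise with their standardised meal". Under Muscle strength and power the article adds: "Prior to any exercise testing participants will be provided with a standardised breakfast". Both places give the same energy and macronutrient content (388 kcal, with 21 g of protein). Neither lists ingredients.

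The Eligibility criteria section says that all interested people are screened for eligibility by telephone. According to the text after the exclusion list, those who agree to take part then receive written and verbal information on procedures, requirements and risks. Written consent follows at the familiarisation visit, before any testing.

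**The concern.** An allergy exclusion exists to keep people away from a product that could harm them. Here the item is tied to the randomised capsules. Whey is a milk protein, is supplied to everyone, and is part of the training procedure. On its stated scope, the item does not prompt a screener to ask about milk.

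What is at stake is the safety of a volunteer with milk-protein allergy who is asked to drink whey at a supervised session. The matter is worth raising because the article already sets out an explicit allergy rule, and that rule is narrower than the set of products the same article says will be given.

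**Working it through.** The check sets the exclusion list against everything the article says participants will consume. The plan gives no figure to reproduce, and no power or sample-size calculation bears on the point.

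**Step 1. Products supplied, and whether the allergy item covers them**

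- PEA capsules (Supplements): covered by name.
- Placebo capsules, stated content maltodextrin (Supplements): covered by name. On the stated content, the placebo wording does not reach milk protein.
- Whey protein concentrate beverage (Resistance training): not covered.
- Standardised meal or breakfast (Supplements; Muscle strength and power): not covered. Ingredients are not stated, so no particular allergen can be attributed to it.

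**Step 2. Number of whey servings**

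Inputs, from Resistance training: 8 weeks of training, 2 sessions per week, one beverage after each session.

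8 x 2 = 16 servings per fully attending participant, in either arm.

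This counts the occasions of exposure. It is not a measure of allergy risk.

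**Step 3. Whether another criterion closes the gap**

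- *Weight-loss programme or particular diet.* The examples are low carbohydrate, ketogenic and vegan, and the list is open-ended. A screener might read it as including a dairy-free diet. A milk-allergic person who otherwise eats normally might honestly answer no. It may catch the person, but not reliably.
- *Chronic disease.* The gastrointestinal part is limited to disorders that impair absorption of nutrients. Milk-protein allergy does not obviously fit.
- *Inability to meet the study's requirements.* Drinking the beverage is a requirement, so this item could exclude someone who cannot take it. It prompts no question about allergy, and works only if the volunteer or screener makes the connection.
- *Recent use of sports supplements or pain medication, smoking, injury, resistance training, functional impairment.* None of these bears on milk allergy.

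**Step 4. Whether the consent stage closes the gap**

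The volunteer is told the procedures and risks before signing, and an allergic adult may well object on learning of the whey. That is self-disclosure after the telephone screen. It is a real safeguard, but not an eligibility rule.

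**Result.** One product supplied to everyone (whey) has a known source, milk, that no criterion names. A second (the meal) has an unstated composition and is likewise outside the allergy item. Two general criteria and the consent discussion may catch an affected volunteer; none is directed at the question.

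**The case against.** The strongest reply is that several safeguards would have to fail together. The diet item is open-ended, the requirements item is broad, and adults aged 18 to 35 are told what they will be asked to do before they consent. This stands. A reader might infer that a milk-allergic volunteer will pass screening and be handed whey; the article does not support that certainty.

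A second reply is that a journal article condenses the full protocol, so the screening form, the plain-language statement and any substitute drink may exist without being shown. This also stands in part: the lack of a described alternative beverage is not a finding. It does not dispose of the point, because the allergy criterion itself is printed and its scope is what falls short.

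A third reply is that limiting an allergy item to the randomised products is a common choice. That may be so, but here the trial itself supplies the other products and specifies when they are taken.

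A reader might also infer damage to the primary lean-mass comparison through dropout or unequal protein intake. The article does not support this. Both arms receive the beverage and the meal, milk allergy precedes randomisation, and any effect is balanced between arms in expectation. Nor does comparing the weight of whey with the weight of the capsules say anything about allergy risk.

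**Conclusion.** The point holds as a limited participant-safety correction. The written allergy exclusion is narrower than the set of products the trial gives, and a milk-allergic volunteer could be enrolled unless caught by the general criteria or by self-disclosure. The exposure would be up to 16 whey servings per participant, assuming full attendance at two sessions a week for 8 weeks.

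The number of people affected cannot be stated, because the article gives no prevalence; the conclusion does not depend on one. It rests on two assumptions: that whey concentrate carries milk protein, and that the printed exclusion list is the rule screeners apply. If the unseen screening form already asks about food allergy, the gap is only in the published wording. The argument concerns allergy and does not extend to intolerance in general. For the meal it goes no further than saying that the ingredients are unstated and the allergy item does not cover them.

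**What to change.** Reconcile the Exclusion criteria with the Supplements, Resistance training and Muscle strength and power sections. Widen the existing allergy item from the capsules to all products the trial supplies, naming at least the whey beverage, and the standardised meal once its ingredients are to hand. Put the question in the telephone screen that already takes place. Because the Trial status section describes recruitment as still ongoing, also ask it once of participants already enrolled. If the screening form already contains the question, only the criterion's wording needs to change.

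The cost is one clause in the criteria, one screening question and one check of current participants. The downside is that a few volunteers may be excluded. No endpoint, sample size or analysis changes.
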